### **17.3 INVESTIGATOR SITE FILE**

The investigator will receive a document folder containing the obligations pertaining to him/her during the clinical investigation. It is mainly composed of:

- CIP (and amendments, if applicable)
- Subject information and informed consent
- Ethics committee documents
- CRFs (incl. diaries/questionnaires)
- Form for serious adverse events and report on device deficiencies
- Study initiation monitoring report
- Monitoring log
- Investigational product accountability documentation
- A copy of ICH-GCP (E6) guideline, Declaration of Helsinki
- Screening list
- Subject identification list
- Site signature and delegation sheet
- Clinical investigation insurance documentation

### **17.4 DATA MANAGEMENT**

All collected data will be documented in the CRF and checked by the monitor at the investigational site at regular intervals for plausibility and completeness according to the monitoring

plan. Suspect or missing entries will be explained by a query list and/or questioning the investigator. The validated data will be stored in an appropriate database.

### **17.5 ARCHIVING**

Source data are a component of the subject records and remain at the investigational site. The completed CRFs will be returned to the CRO for data entry and archived along with other study documentation and correspondence concerning the study (Trial Master File) by the sponsor. The ISF including copies of CRFs will remain at the investigational site. The documents will be retained at least 10 years after the end of the clinical investigation.

### **17.6 PRESENTATION OF DATA – FINAL REPORT**

At the end of the clinical investigation, the CRO will write a study report in alignment with the ISO 14155.

## **18 FINANCING / INSURANCE**

The financial sponsor of this clinical investigation is Enzymatica AB. For the event of an injury arising from participation in the clinical investigation, all subjects are covered by a clinical investigation insurance.

## **19 PUBLICATION POLICY**

The results of this clinical investigation may only be published with the written agreement of the study sponsor.

## 21.2 STUDY FLOW CHART

| Procedure/
Assessment                                               | Visit 1
Screening /
Randomisation | Visit 2
on day 2–3 after
start of IP use | Visit 3
Final visit*
16 ± 4 days after
start of IP use |
|------------------------------------------------------------------------|-----------------------------------------|------------------------------------------------|-----------------------------------------------------------------|
| Subject information                                                    | X                                       |                                                |                                                                 |
| Written informed consent                                               | X                                       |                                                |                                                                 |
| Anamnestic, demographic data                                           | X                                       |                                                |                                                                 |
| Inclusion and exclusion criteria                                       | X                                       |                                                |                                                                 |
| Medical history/
concurrent diseases                                | X                                       |                                                |                                                                 |
| Concurrent treatment                                                   | X                                       | X                                              | X                                                               |
| Physical examination                                                   | X                                       | X                                              | X                                                               |
| Blood pressure and pulse rate                                          | X                                       | X                                              | X                                                               |
| Documentation of cold symptoms                                         |                                         | X                                              |                                                                 |
| Urinalysis incl. pregnancy test for
women of childbearing potential | X                                       |                                                |                                                                 |
| Issue of subject diary and instruc-
tion                            | X                                       |                                                |                                                                 |
| Check of subject diary                                                 |                                         | X                                              |                                                                 |
| Return/control of subject diary                                        |                                         |                                                | X                                                               |
| Randomisation                                                          | X                                       |                                                |                                                                 |
| Issue of IP** and instruction                                          | X                                       |                                                |                                                                 |
| Collection of IP and accountabil-
ity**                             |                                         |                                                | X                                                               |
| Adverse events                                                         | X                                       | X                                              | X                                                               |
| Device effects                                                         |                                         | X                                              | X                                                               |
| Global evaluation of efficacy, tol-
erability and safety by subject |                                         |                                                | X                                                               |

\* subjects with early termination or without cold symptoms during the entire study duration would only have terminal visit (TV) comprising the assessment of AEs and concurrent treatment as well as the return of IP and diary

\*\* verum group

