|                           | 
first IP use (for verum group), the subject should attend a visit on site (V2) and get an examination by the investigator.
 
Between V1 and V2, the study centre will have monthly phone contact with the subjects as a reminder about the study.
 
The termination visit (V3) will take place on day 16 (+/-4 days) after first IP use.
 
Subject with no symptoms during the study period will only have the termination visit (TV) at a time point of 16 weeks (+/-7 days) after V1.
                                                                                                                                                                                                                                                                                                                                                                                                                                                                                                                                                                                      |
| Duration of intervention: | 
The IP use (verum group) should start when following conditions have been fulfilled:
 
 
• answering "Yes" to either of the questions in the subject diary: "Do you think/feel you have a cold?" or "Do you think/feel you are coming down with a cold (might be having first signs of cold)?"
 
• Jackson score of at least 1 (mild = sensible, but not disturbing or irritating) for any symptom except headache
 
 
The IP should be used until 2 days after the subject is symptom free (=answering "No" to the question "Do you think that you are still sick with this respiratory infection?" for 2 days in a row), but not longer than 12 days in total.
 
The following treatment is defined as optional care to be applied as needed during the common cold period:
 
 
• paracetamol (max. 2 g/day),
 
• ibuprofen (max. 400 mg/day),
 
• sea water nose drops or nose spray
 
• as well as antibiotics (in case they are necessarily required).
 
 |

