### **12.3 VISIT 3 (V3, FINAL), 16 +/-4 DAYS AFTER SYMPTOM START**

- Questioning and documentation of possible occurrence of AEs/device deficiencies
- Questioning and documentation of new or changed concurrent treatment
- Return and control of the subject diary by a study team member (except investigator)
- Return of IP (verum group) and accountability
- Physical examination
- Measurement of blood pressure and pulse rate

- Global evaluation of efficacy by subjects (4-point categorical scale)
- Global evaluation of safety and tolerability by subjects (4-point categorical scale)

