## **12.4 TERMINATION VISIT (TV) FOR SUBJECTS WITH NO SYMPTOMS DURING THE STUDY PERIOD, 16 WEEKS +/-7 DAYS AFTER V1**

- Questioning and documentation of possible occurrence of AEs
- Questioning and documentation of new or changed concurrent treatment
- Return of the subject diary
- Return of IP (verum group)

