## **12.8 ASSESSMENT OF SAFETY**

### **12.8.1 Blood Pressure and Pulse Rate**

Sitting blood pressure and pulse rate will be measured using standard products and procedures at all study visits.

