### **12.10.1 Withdrawal of Subjects**

Reasons for subject's withdrawal may be for example:

- Serious adverse event (SAE)
- Intolerance of the investigational product
- Required additional therapy due to other complaints, which could influence the safety of the subject or the results of the study
- Clinically significant illness or intake of concurrent medication according to exclusion criteria, which could influence the results of the study
- Subject is not compliant with study requirements (according to investigator judgement)
- Withdrawal of informed consent
- Subjects in the study once the number of treated subjects has been completed

Reason, time and specific details of a subject's withdrawal are documented in the CRF. Each subject who terminates the study prematurely will be asked to undergo the final visit (corresponding to Visit 3) to be documented in the CRF.

If possible, the IP should be returned by the subject. Subjects who discontinue due to safety reasons should, whenever possible, be seen and assessed by the investigator and be medically treated as appropriate.

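### The protocol sends early terminators to two different final visits; under the flow-chart footnote, product users who stop early give no global safety or efficacy rating

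*Protocol*

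**What the plan says.** Section 12.10.1 (Withdrawal of Subjects) covers everyone who leaves early: "Each subject who terminates the study prematurely will be asked to undergo the final visit (corresponding to Visit 3". Its example reasons include a serious adverse event, intolerance of the investigational product (IP), withdrawn consent, and still being in the study when the target number of treated subjects has been reached.

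The flow chart in section 21.2 marks its Visit 3 (V3) column with a footnote: "subjects with early termination or without cold symptoms during the entire study duration would only have terminal visit (TV". It then gives the content of that termination visit (TV): "comprising the assessment of AEs and concurrent treatment as well as the return of IP and diary".

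The TV is defined more narrowly elsewhere. The title of section 12.4 is "TERMINATION VISIT (TV) FOR SUBJECTS WITH NO SYMPTOMS DURING THE STUDY PERIOD", and the Synopsis says "Subject with no symptoms during the study period will only have the termination visit (TV". Neither sends early terminators to it.

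Section 12.3 puts more into V3 than the TV holds, including "Questioning and documentation of possible occurrence of AEs/device deficiencies" and "Global evaluation of safety and tolerability by subjects (4-point categorical scale". It also has a physical examination, blood pressure and pulse, IP accountability and a global efficacy rating. Sections 12.7.2 and 12.8.3 take the global ratings from the verum group only.

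**The concern.** For a subject who used the IP and then left the study, section 12.10.1 and the footnote prescribe different visits. The footnote says that these subjects have only the TV, so it cannot be read as a minimum to which the V3 items are added. Section 12.10.2 refers back to the same withdrawal rules if the whole investigation is stopped, so the conflict would carry over to that case.

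Subjects who stop because they do not tolerate the spray say the most about how well it is tolerated. If they are not asked for the global rating, the reported distribution rests mainly on people content enough to finish. The control group gives no such rating, so nothing in the data would reveal the selection. Staff working from the flow chart and staff working from section 12.10.1 would also collect different data on the same kind of subject. An analysis plan cannot repair this, because a rating that was never collected cannot be recovered.

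**Working it through.** The protocol gives no figure on this point to reproduce. The check sets the visit contents side by side.

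| Item | V3 (12.3) | TV (12.4 and footnote) | Rule elsewhere |
|---|---|---|---|
| Adverse events | yes | yes | serious events within 24 hours (13.2.3) |
| Concurrent treatment | yes | yes | – |
| Return of IP and diary | yes | yes | – |
| IP accountability | yes | not listed | done on collected IP (10.4) |
| Physical examination | yes | not listed | all visits (Synopsis) |
| Blood pressure, pulse | yes | not listed | all visits (Synopsis, 12.8.1) |
| Device deficiencies | yes | not listed | every examination after IP use (13.2.2); V2 and V3 (Synopsis, 7.2) |
| Global efficacy rating | yes | not listed | V3 only (Synopsis, flow chart) |
| Global safety/tolerability rating | yes | not listed | V3 only (Synopsis, flow chart) |

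**Who the TV was written for.** Under section 10.2, IP use starts only at symptom onset. Subjects with no symptoms therefore have no IP experience to rate, and a short visit is coherent for them. The footnote is the only place that extends the TV to people who may have used the IP.

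**Which gaps are covered elsewhere.** For vital signs, section 12.8.1 is general: "Sitting blood pressure and pulse rate will be measured using standard products and procedures at all study visits". The Synopsis says the same and adds the physical examination, and section 13.2.2 does it for device deficiencies. For these items the TV list conflicts with rules that would call for them. For the two global ratings no such rule exists: the visit-level schedules name V3 alone.

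**Who counts as an early terminator.** Section 9.1 expects 300 randomised and 200 treated, so 300 − 200 = 100 would not enter the treatment phase (80 to 120 with the allowed deviation of 20). Some of these complete 16 weeks without symptoms. Others may be withdrawn once the target is met, and the protocol does not give the split. The term therefore mixes IP users with never-users. Section 12.10.1 is too wide for the second group, since a V3-type visit would ask a verum subject to rate a product never used.

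**Direction and size of the effect on the ratings.** Let w be the share of IP users who stop early and are not asked, f_c the proportion with a favourable rating among those asked, and f_e the proportion among those not asked. The reported figure is f_c and the figure for all users is (1 − w)·f_c + w·f_e. The difference is w·(f_c − f_e), positive whenever early stoppers would rate worse than the rest. The protocol gives neither w nor f_e.

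An illustration, all of it assumed, takes 100 IP users of whom 90 would rate favourably:

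- 5 not asked, all 5 unfavourable: 90/95 = 94.7%
- 5 not asked, 3 unfavourable: 88/95 = 92.6%
- 10 not asked, all 10 unfavourable: 90/90 = 100%
- 10 not asked, 6 unfavourable: 86/90 = 95.6%
- those not asked rate like the rest: 90%, unchanged

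The answer runs from no distortion to complete distortion, depending on inputs that the protocol does not supply.

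**The case against.** The strongest defence is that little is truly lost. Adverse events are asked at the TV, and serious ones are reported within 24 hours whatever the visit. Vital signs, physical examination and device deficiencies are covered by the general rules above, and anyone who stops after Visit 2 already has all three from that visit. Section 12.10.1 also asks that subjects who stop for safety reasons be seen and assessed by the investigator whenever possible. V3 contains every TV item, so a site that runs a V3-type visit delivers all the TV content. The footnote may have been written with untreated subjects in mind, those withdrawn at the target number. The trial is an exploratory pilot, and the ratings are unblinded, uncontrolled and not among its main endpoints.

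Most of this stands. A reader might infer that the flow chart discards safety data generally, or that device deficiencies in early stoppers are never collected. The documents do not support either reading, given sections 12.8.1 and 13.2.2, Visit 2 and the adverse-event rules. A reader might also want to put a number on the bias, such as 90% favourable turning into 95% to 100%. That needs an invented stopping rate of 5% to 10%, and every subject lost would have to rate unfavourably. Nor does the text show an intention to skip ratings from IP users.

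Three things survive. The safeguard for safety discontinuations names no V3 item, so it does not secure the rating. Sections 7.1, 7.2 and 12.7.2 place ratings at study end, which could be stretched to a subject's own last visit, but the footnote lists the TV content and no rating is in it. The footnote's wording covers all early terminators, whatever group it was meant for.

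**Conclusion.** The contradiction is real and lies in current text: section 12.10.1 and the flow-chart footnote prescribe different visits for the same subjects, and the footnote also departs from section 12.4 and the Synopsis. The firm consequence is narrow. Where the footnote is followed, IP users who stop early give no global safety/tolerability or efficacy rating, and the verum-only ratings would tend to look too favourable. That direction assumes that early stoppers would rate worse than completers. Its size cannot be estimated, because the protocol states no early-termination rate. The missing examination, vital signs and device-deficiency questions are a further inconsistency with sections 12.8.1 and 13.2.2 and the Synopsis, not a demonstrated loss. Adverse-event reporting and the main endpoints are not shown to be affected. The point should be corrected because it changes what is collected; it does not threaten the trial's main purpose.

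**What to change.** Reconcile sections 12.4 and 12.10.1 and the footnote in section 21.2 so that one list of assessments applies to early termination, split by exposure:

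- **Subjects who used the IP:** collect the section 7.2 safety parameters, explicitly including the global safety/tolerability rating and the device-deficiency question, whichever visit name is kept. State whether the global efficacy rating is taken as well.
- **Subjects who never had symptoms or never used the IP**, including those withdrawn once the treated number is reached: state which reduced list applies and leave out ratings of a product they did not use.

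Also align the TV list with the all-visits rules in the Synopsis and section 12.8.1, either by adding the items or by exempting the TV expressly. The cost is revised wording in a few places. No visit is added, since early terminators are already asked to attend one.
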